## **7. Statistical analysis**

Statistical analysis will follow intention to treat. Data from children who participate in at least 1 follow-up visit will be included in the analysis. All statistical analyses will be performed using SPSS (IBM Corp, NY, USA) and R (R Foundation for Statistical Computing, <https://www.R-project.org/>). A two-sided *P*-value <0.05 will be considered statistically significant.

Eye-specific outcome measures will be compared between treatment groups using generalized linear models and generalized estimating equations (GEE) will be used to account for inter-eye correlation. Person-level categorical outcomes will be compared between two treatment groups using chi-square test. For comparing the longitudinal changes of outcome measures

between two treatment groups, GEE models with an autoregressive correlation structure will be used. This longitudinal analysis using GEE will include data from all participants including those who withdraw from the trial during the follow-up.

For the change in SE, AL, and choroidal measures, subgroup analyses will be performed for age ( $\leq 8$  years vs.  $> 8$  years), sex (male vs. female), baseline SE ( $\leq -2$  D vs.  $> -2$  D), baseline AL ( $\leq 24$  mm vs.  $> 24$  mm), distant magnitude of exodeviation at baseline ( $\leq 20$  PD vs.  $> 20$  PD) and daily outdoor hours ( $\leq 2$  hours vs.  $> 2$  hours). The differences in treatment effect between subgroups will be evaluated based on the test of interaction between treatment group and subgroup.

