### 5.5 Eligibility

#### Inclusion criteria

- 1) age 6-12 years old;
- 2) basic-type IXT meeting all the following criteria:

- (a.) intermittent or constant exotropia at distance (6 m), and either an IXT or exophoria at near (33 cm);
  - (b.) exodeviation magnitude of  $\geq 10$  prism diopters (PD) at distance measured by the prism and alternate cover test (PACT);
  - (c.) near/distance deviation difference of  $\leq 10$  PD;
- 3) myopia  $\leq -0.5$  diopters (D) and  $> -6$  D in both eyes based on cycloplegic spherical equivalent (SE);
  - 4) distant best-corrected visual acuity (BCVA) of  $\leq 0.2$  logarithms of the minimum angle of resolution (logMAR) in each eye as measured using Early Treatment for Diabetic Retinopathy Study (ETDRS) charts.

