## **5.6 Sample size**

The sample size is determined using PASS 15 (NCSS, Utah) assuming: (1) the annual reduction of SE as 0.59 D in the 0.01% atropine group and 0.81 D in the control group according to results of the LAMP study; (2) the common standard deviation (SD) is assumed as 0.57 D in each group; (3) randomization to 0.01% atropine group and placebo control group is 2:1. The trial needs 160 participants in the 0.01% atropine group and 80 participants in the control group to provide 80% power (at 5% type I error rate) for detecting a clinically relevant difference of 0.22 D in SE progression at 12 months. To account for an expected drop-out rate of 20% over the 12 months follow-up period, the total number of participants for enrollment is 300 participants (200 in 0.01% atropine group and 100 in placebo control group).

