## **5.7 Randomization and masking**

Eligible participants will be 2:1 randomized to receive 0.01% atropine or placebo eyedrops by use of a block randomization scheme with a fixed block size of six. Randomization will be completed by one unmasked investigator using sealed envelopes that contain randomized numbers. The random allocation sequence is generated using randomized block methods in the

Statistical Package for the Social Sciences (R Foundation for Statistical Computing. <https://www.R-project.org/>) by a statistician who is not involved in participant recruitment or data collection. Other investigators, participants, and the statistician will be masked to study allocation.

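### The primary model for 1-year SE change pre-specifies no adjustment for age or baseline SE, which forgoes precision or leaves the covariate set open

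*Combined protocol and SAP*

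**What the plan says.** Section 7 (Statistical analysis) gives the method for the primary outcome in one sentence: "Eye-specific outcome measures will be compared between treatment groups using generalized linear models", with GEE handling the two eyes of a child. A further GEE with an autoregressive structure is planned for longitudinal changes. Neither sentence lists a covariate or says whether the model is adjusted or unadjusted, and no other section supplies an adjustment set.

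Section 5.7 describes a "block randomization scheme with a fixed block size of six", allocated 2:1, and mentions no stratification factor.

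Section 5.5 admits a broad population: "age 6-12 years old", with cycloplegic SE from -0.5 D to just short of -6 D.

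Section 7 does name age (cut at 8 years) and baseline SE (cut at -2 D) as subgroup factors for SE change, with interaction tests. That is their only stated use in the analysis.

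Section 5.6 sizes the trial as a plain comparison of two means, taking "the annual reduction of SE as 0.59 D in the 0.01% atropine group and 0.81 D in the control group" and stating that "the common standard deviation (SD) is assumed as 0.57 D in each group". It makes no allowance for covariates.

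**The concern.** By choosing age and baseline SE as subgroup factors for SE change, the plan signals that both may bear on progression. A subgroup interaction test asks whether the treatment effect differs between strata. It does not remove the variance these factors explain from the primary comparison, and it does not correct that estimate for a difference between arms at baseline. Randomisation in blocks of six controls group sizes, not the distribution of age or SE.

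The section 7 text can be read in two ways, and each has a cost.

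- **Group-only model.** Any variation in progression explained by age and baseline SE stays in the residual. The confidence interval is then wider than it need be, and a chance difference in age between arms is carried in the estimate.
- **Open model.** A generalized linear model fitted by GEE can carry covariates. If none are fixed in advance, the set can be chosen once results are visible, and this concerns the primary result.

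**Working it through.** **Inputs from the documents.** Target difference 0.81 - 0.59 = 0.22 D; SD 0.57 D; two-sided 5% level; 160 atropine and 80 placebo evaluable; 20% drop-out (sections 5.6 and 7). As in section 5.6, one value per child is used.

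**Inputs assumed, because the documents do not give them.** R² of age plus baseline SE for 1-year SE change, 0 to 0.30; age SD 1.7 years; slope of SE change on age 0.10 D per year.

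**1. The plan's own figure.**
- SE of the unadjusted difference = 0.57 × √(1/160 + 1/80) = 0.57 × 0.1369 = 0.078 D.
- Power at 160/80 is 80.5% by the normal approximation and 80.2% by the noncentral t.
- Enrolment = 240 / (1 - 0.20) = 300, that is 200 + 100.
- The stated design reproduces with no covariate adjustment.

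**2. Power with adjustment.** Residual SD = 0.57 × √(1 - R²), at 160/80, noncentral t. The last column is 240 × (1 - R²), the evaluable number that would give the planned power.

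| Assumed R² | Residual SD (D) | Power | Evaluable N for planned power |
|---|---|---|---|
| 0 | 0.570 | 80.2% | 240 |
| 0.05 | 0.556 | 82.1% | 228 |
| 0.10 | 0.541 | 84.1% | 216 |
| 0.20 | 0.510 | 88.1% | 192 |
| 0.30 | 0.477 | 91.9% | 168 |

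The gain runs from nothing to about 12 percentage points.

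**3. Chance imbalance in age.**
- SE of the difference in mean age = 1.7 × 0.1369 = 0.233 years.
- A 1-SE imbalance shifts the unadjusted estimate by 0.233 × 0.10 = 0.023 D, about 10% of 0.22 D.
- A 2-SE imbalance shifts it by 0.047 D, about 21% of 0.22 D and 60% of the 0.078 D standard error. Imbalance of at least that size, in either direction, arises in about 5% of randomisations.
- These inputs imply an R² for age alone of (0.10 × 1.7)² / 0.57² = 0.0289 / 0.3249 = 0.09, so the higher rows of the table also need a contribution from baseline SE.

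**4. The open reading.** I simulated the null at 160/80 with two equally prognostic covariates. Each model, fixed in advance, rejected in about 5% of runs. Taking the smallest p-value among four models (neither covariate, either one, both) rejected in roughly 7, 8 and 9% at an assumed R² of 0.10, 0.20 and 0.30. This shows what an unspecified set permits; it does not predict what the sponsor would do.

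**The case against.** Three stronger readings are tempting, and the documents support none of them.

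- **That the primary analysis is unadjusted.** Section 7 never says so. It is silent, and the method it names can take covariates. What can be shown is that no adjustment is pre-specified.
- **That the trial is underpowered.** It is not. Section 5.6 assumes no covariate gain, and its 80% target is met at 160/80. What is lost is optional precision.
- **That chance imbalance biases the comparison or inflates the type I error.** Under randomisation the unadjusted test keeps its level, and its standard error already allows for such imbalance. The argument concerns the estimate conditional on the imbalance that occurs.

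It is also fair to say that the gain cannot be sized from the documents: at R² = 0.05 it is about 2 points, and at zero there is none. The outcome is already a change from baseline, which removes differences in baseline level, though not any link between baseline SE and rate of progression. Finally, a sentence stating that the model is unadjusted would close the pre-specification gap by itself.

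All of this stands and limits the point. It leaves the central observation intact: the plan fixes no covariate set for its primary result, and two candidate covariates are already collected at baseline.

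**Conclusion.** The concern holds as a gap in pre-specification with a probable cost in precision. The trial is valid without the change, so this is an improvement the sponsor should make rather than a fatal defect. Its size depends on an R² that the documents do not give: no gain at zero, about 84% power at 0.10, about 92% at 0.30, against 80.2% unadjusted. The age shifts of about 0.02 D (1 SE) and 0.05 D (2 SE) depend on the assumed age SD and slope and would scale with either. Nothing here has been worked out for the secondary outcomes, so the conclusion is confined to the primary comparison.

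**What to change.** In section 7, define the primary analysis as the between-group difference in cycloplegic SE change at 12 months, estimated from the GEE model with treatment, baseline age (continuous) and that eye's baseline cycloplegic SE (continuous) as covariates, and with the child as the cluster. Report the unadjusted difference as a sensitivity analysis.

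This costs a sentence or two of wording and no new data, since age and cycloplegic refraction are both recorded at baseline. It must be settled before unmasking. The documents do not show the trial's present status; if allocation has already been revealed, the adjusted result should be labelled as not pre-specified.

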### **5.9.2 Secondary outcomes**

- 1) Cycloplegic SE change from baseline at 2 years.
- 2) Change from baseline in axial length, monocular function (BCVA, near vision, accommodative amplitude [AA] and photopic/mesopic pupil size), exotropia conditions (distant/near magnitude of exodeviation and distant/near exotropia control), binocular vision (distant/near stereoacuity, near point of convergence [NPC], accommodative convergence/accommodation [AC/A] ratio, and fusional vergence amplitude [FVA]) and safety parameters (intraocular pressure [IOP] and corneal endothelial cell density [ECD]) at 1 year and 2 years.
- 3) Change in choroidal parameters and higher-order aberrations.

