276 **12) Distant and near control**

277 ⑩ IXT office control scale ranging from 0 (phoria, best control) to 5 (constant  
278 exotropia, worst control) at both distance and near fixation.

279 ⑩ Intermittent Exotropia Control Scale:

280 5 = Constant exotropia

281 4 = Exotropia > 50% of the exam before dissociation

282 3 = Exotropia < 50% of the exam before dissociation

283 2 = No exotropia unless dissociated, recovers in > 5 seconds

284 1 = No exotropia unless dissociated, recovers in 1–5 seconds

285 0 = No exotropia unless dissociated, recovers in < 1 second (phoria)

Levels 5 to 3 are assessed during an initial 30-second period of observation. Levels 2 to 0 are graded as the worst of three rapidly successive trials. An occluder is placed over the right eye for 10 seconds and then removed, measuring the length of time it takes for fusion to become re-established. The left eye is then occluded for a 10-second period and the time to re-fusion is similarly measured. A third trial of 10-second occlusion is performed, covering the eye that required the longest time to re-fuse. The worse level of control observed following the 3, 10-second periods of occlusion should be recorded for that visit.

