### **13) Distant stereoacuity**

- ⑩ Random Dots Distant Test (P/N 1006, Vision assessment Corporation, Illinois, USA)
- ⑩ 3 meters
- ⑩ Ranging from 63 to 400 arcsecs (log stereoacuity values, 1.8 to 2.6 log arcsecs)
- ⑩ Subjects unable to identify shapes at the 400 arcsecs level are recorded as having 'nil' stereo (log stereoacuity value, 3.2 log arcsecs).

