### **14) Near stereoacuity**

- ⑩ Randot Preschool Stereoacuity test (Stereo Optical Co., Inc, Illinois, USA)
- ⑩ 40 cm
- ⑩ Testing disparities at 800, 400, 200, 100, 60 and 40 arcsecs
- ⑩ The result is recorded as the smallest disparity at which the subject could correctly identify at least two of the three shapes.

309 ⑩ Participants who are unable to identify the largest disparity (800 arcsecs)  
310 are recorded as having 'nil' stereo (log stereoacuity value, 3.2 log  
311 arcsecs).

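### Section 7 does not say how the ordered 0–5 exotropia control scores will be analysed; if its chi-square rule is applied, the ordering is ignored and power falls.

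*Combined protocol and SAP*

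**What the plan says.** Section 7 contains three rules for comparing the arms.

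- Eye-specific measures go to generalized linear models, with GEE to handle the correlation between a child's two eyes.
- "Person-level categorical outcomes will be compared between two treatment groups using chi-square test". No list of these outcomes follows.
- For longitudinal change in outcome measures, "GEE models with an autoregressive correlation structure will be used". The link, the distribution and any covariates are not given.

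Section 5.11, item 12, describes the control measure as an "IXT office control scale ranging from 0 (phoria, best control) to 5". It has six ordered grades, and each child gets one grade at distance and one at near. Section 5.9.2 opens its second group of secondary outcomes with "Change from baseline in axial length, monocular function" and includes in it "exotropia conditions (distant/near magnitude of exodeviation and distant/near exotropia control", at 1 and 2 years. Section 4.2.1 makes the effect on exotropia conditions the key secondary objective.

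Stereoacuity (Section 5.11, items 13 and 14) is recorded in log arcsec. A child who fails the coarsest plate is coded 3.2 on both tests. The coarsest distance plate is 400 arcsec. The near test is listed as "Testing disparities at 800, 400, 200, 100, 60 and 40 arcsecs".

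**The concern.** The control score is not eye-specific, so the first rule does not fit it. Of the two that remain, the chi-square rule matches it most closely as a graded, person-level outcome compared at a time point. A Pearson chi-square treats the six grades as unordered labels: a shift of one grade across the whole arm counts no more than a patternless scatter of the same size. It yields a p-value but no signed effect and no interval, and it has no place for the baseline score as a covariate.

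This outcome is a poor place for an insensitive test. Section 3 says that earlier trials excluded children with strabismus and that atropine's influence on exotropia is unknown. A non-significant result on control could therefore be read as reassurance. If the GEE is meant instead, the reader still cannot tell whether the score is modelled as ordinal or numeric, or whether baseline is adjusted for. That choice would then be open after the data are seen.

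**Working it through.** **1. The plan's own figure.** The only power statement, in Section 5.6, concerns the primary outcome: difference 0.22 D, SD 0.57 D, 2:1 allocation, two-sided 5%, 80% power.

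Control arm n = (1.96 + 0.8416)² × 0.57² × (1 + 1/2) / 0.22² = 7.85 × 0.3249 × 1.5 / 0.0484 ≈ 79.0, taken up to 80. The atropine arm is then 160 and the total 240, and 240 / 0.8 = 300. This reproduces the plan (power at 160/80 is 80.5%). No power is stated for the control score.

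**2. Cost of ignoring order, analytically.** Suppose a 1-df ordered test has 80% power. Its noncentrality is λ = (1.96 + 0.8416)² = 7.85. An unordered chi-square on k occupied grades sees the same λ on k − 1 df, so its power is P(χ²(k − 1, λ) > the 95th percentile of χ²(k − 1)). This assumes that the treatment effect lies wholly along the ordering.

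| Occupied grades | df | Chi-square power | Relative loss |
|---|---|---|---|
| 6 | 5 | 55.5% | (80 − 55.5)/80 = 31% |
| 5 | 4 | 59.5% | (80 − 59.5)/80 = 26% |
| 4 | 3 | 64.5% | (80 − 64.5)/80 = 19% |
| 3 | 2 | 70.9% | (80 − 70.9)/80 = 11% |

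**3. Simulation at 160 vs 80.** A latent normal score was cut into ordered grades, with 1,500 replicates per setting (Monte Carlo standard error near 55% power: √(0.55 × 0.45/1500) ≈ 1.3 points). The shift, the baseline correlation and the grade distributions are assumptions, because the documents supply none.

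- *Six grades, shift 0.4 SD, baseline correlation 0.3 to 0.7, three distributions (even, mid-heavy, skewed to good control).* Chi-square on follow-up grades has 53–58% power, Mann-Whitney 72–81%, and linear ANCOVA adjusted for baseline 79–96%. The relative loss is 24–32% against Mann-Whitney and 27–42% against ANCOVA.
- *Four grades, same shift.* The loss is 18–19% against Mann-Whitney and 22–35% against ANCOVA.
- *Six grades, mid-heavy distribution, correlation 0.5, shift 0.3 SD.* Chi-square 35.7% against ANCOVA 71.3%, a loss of about 50%.
- *The same with shift 0.5 SD.* Chi-square 79.2%, Mann-Whitney 93.7%, ANCOVA 98.5%, losses of about 15% and 20%.
- *Chi-square on categories of change, six grades, shift 0.4 SD.* Power is 25–68%. This uses baseline but still ignores order.

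**4. Stereoacuity code.** log₁₀ 400 = 2.60 and log₁₀ 800 = 2.90. One octave is log₁₀ 2 = 0.30. At distance, 3.2 − 2.6 = 0.6, or two octaves beyond the last plate. At near, 3.2 − 2.9 = 0.3, or one octave. The same code is therefore a larger step at distance than at near.

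**The case against.** The strongest objection is that the plan never sends the control score to chi-square. Section 7 does not name its categorical outcomes, and elimination cannot settle the matter: exodeviation in prism diopters, near point of convergence, the AC/A ratio and fusional amplitude are person-level and numeric, and fit neither of the first two rules. The longitudinal GEE rule is not confined to eye-specific measures, and control is graded at every visit. A GEE on the numeric score would use its order and give a signed estimate. This stands: assignment to chi-square is the closest reading, not a stated fact. It does not remove the gap, because the GEE route names no ordinal form and no baseline term.

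A reader might also infer that the baseline score is thrown away. The documents do not support that. Section 5.9.2 defines the outcome as a change from baseline, and a chi-square on change categories would use it. What is missing is baseline adjustment.

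A flat loss of about a third of the power is tempting too. It holds only near six occupied grades and an ordered test at 80% power. Section 5.5 makes six well-filled grades doubtful at entry: near deviation must be intermittent exotropia or exophoria, which rules out grade 5 at near, and distance deviation must be a manifest exotropia, which makes grade 0 doubtful there. Five grades give 26%. Occupancy at follow-up is unknown.

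Finally, the proportions in a chi-square table do show which arm is worse, and exodeviation magnitude also captures worsening. Both are fair. Neither supplies an effect estimate with an interval for control.

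**Conclusion.** The concern holds in conditional form. The plan leaves the analysis of a component of the key secondary objective unstated, and the rule that fits it best is blind to order. If that rule is applied, the relative loss of power is about 11–31% against an ordered test at 80% power, depending on whether three or six grades are occupied. It is larger in some assumed settings against a baseline-adjusted analysis, up to about 50% with a small shift. The analytic figures assume an effect along the ordering, and all simulated figures rest on assumed distributions, shifts and correlations.

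Stereoacuity is a secondary point only. One might infer that mean log change will be analysed and that the nil code will drive it. The documents state no such analysis and give no share of nil results, so all that can be said is that a mean would be sensitive to an unequal top code if it were used. The primary outcome and the sample size of 300 are not affected.

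**What to change.** In Section 7, name the analysis for distance and near control at 12 and 24 months: a proportional-odds model of the control grade on treatment and baseline control score, or an ordinal GEE across visits with the same terms. Report the common odds ratio with its 95% CI, and add a rank test as a sensitivity analysis. State which outcomes count as person-level categorical, and keep chi-square for those that are unordered or yes/no. If mean log change is used for stereoacuity, add an ordinal or rank analysis as sensitivity, since neither depends on the value chosen for nil.

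The cost is SAP wording, with no new data, visits or participants. The downside is the proportional-odds assumption, which the rank test partly covers.

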| Mydriatic fundus examination (Volk Digital Wide Field Lens)                              | √ |   |   | √ |   | √ |   | √ |   | √ |
| Dispensation of study medication/dosing compliance diary and symptom inquiry             | √ | √ | √ | √ | √ | √ | √ | √ | √ | √ |

|                              |   |   |   |   |   |   |   |   |   |   |
|------------------------------|---|---|---|---|---|---|---|---|---|---|
| Daily activity questionnaire | √ | √ | √ | √ | √ | √ | √ | √ | √ | √ |
|------------------------------|---|---|---|---|---|---|---|---|---|---|

236 **5.11 Clinical examinations**

237 **1) Noncycloplegic refraction**

238 ⑩ Topcon KR-8900 (Topcon Corp, Tokyo, Japan) and manual refraction

239 **2) BCVA**

240 ⑩ ETDRS charts (Good-Lite Company, Illinois, USA)

241 ⑩ 4 meters

242 ⑩ With the manual refraction and trial frames

243 **3) Near vision**

244 ⑩ Illiterate “E” charts (Precision Vision, Sussex Vision Intl. Ltd, West Sussex,  
245 UK)

246 ⑩ 40 cm

247 ⑩ With the manual refraction and trial frames

248 **4) Slit lamp biomicroscopy**

249 ⑩ To evaluate the eyelid, eyelashes, conjunctiva, cornea, anterior chamber,  
250 iris, pupil, lens, and anterior vitreous

251 **5) Non-mydriatic fundus examination**

252 ⑩ FundusVue (Crystalvue Medical Corporation, Taiwan, China)

253 ⑩ To provide color retinal image

254 **6) Biometry before cycloplegia**

255 ⑩ Zeiss IOL Master 700 (Carl Zeiss Meditec Inc, Dublin, CA)

256 ⑩ To obtain ocular parameters, including AL

257 **7) Accommodative amplitude (AA)**

258 ⑩ Near point rule (rod with a moveable target and metric markings)

259 ⑩ Monocularly

260 ⑩ With the manual refraction and trial frames

261 ⑩ The near point of accommodation is determined when the participant  
262 reports that the letters become blurred, and clarity can not be regained,  
263 when the target is moved towards the participant's eyes.

264 **8) Photopic and mesopic pupil size**

265 ⑩ OPD-Scan III (Nidek, Gamagori, Japan)

266 ⑩ Average of at least 5 consecutive measures

267 **9) Intraocular pressure (IOP)**

268 ⑩ ICare rebound tonometer (Icare Finland Oy, Helsinki, Finland)

269 ⑩ Average of 3 IOP values

270 **10) Corneal endothelial cell density**

271 ⑩ Topcon SP-1P (Topcon Corp, Tokyo, Japan)

272 **11) Distant/near magnitude of exodeviation**

273 ⑩ PACT

274 ⑩ Accommodative targets for fixation at distance (6 m) and near (33 cm)

275 ⑩ Measure after 1 hour of monocular occlusion using a patch.

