**20) Cycloplegic autorefraction**

⑩ Topcon KR-8900 (Topcon, Tokyo, Japan)

⑩ Instill 6 drops of 1% tropicamide at a 5-minute interval and measure after another 10-minute rest.

⑩ Further cycloplegic eyedrops should be given if the pupillary light reflex is still present or the pupil size is less than 6.0 mm ten minutes after the last eyedrop.

All the procedures will be performed by trained ophthalmologists and optometrists, who are masked for the treatment assignment.

At baseline, the participant will be prescribed best-corrected spectacles if the ones worn are inappropriate for either a difference of spherical power or cylinder power exceeding 0.25D. Participants will be inquired whether photophobia exists at baseline, because some IXT patients may have the symptom.

Daily outdoor hours and self-report symptoms related to allergy, blurred near vision, photophobia, or any discomfort are inquired at each visit.

During the follow-up, if a participant has non-serious ocular events e.g., bacterial or allergic conjunctivitis, the guardian should contact the investigator and stop using eyedrops under the investigator's guidance. This duration of

stopping treatment should not exceed 4 weeks (28 days).

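### Section 7 runs at least 18 unadjusted subgroup interaction tests per time point, cuts five scaled modifiers in two, and does not tie outdoor hours to baseline

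*Combined protocol and SAP*

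**What the plan says.** The subgroup paragraph of section 7 (Statistical analysis) opens with "For the change in SE, AL, and choroidal measures, subgroup analyses will be" and lists six two-level factors: age (cut at 8 years), sex, baseline SE (-2 D), baseline AL (24 mm), "distant magnitude of exodeviation at baseline" (20 PD) and daily outdoor hours (2 hours). Differences in treatment effect between subgroups are judged by a "test of interaction between treatment group and subgroup".

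The only decision rule in section 7 is that a two-sided P-value below 0.05 "will be considered statistically significant". The section gives no multiplicity rule, no ordering of tests, no exploratory label and no time point for the subgroup analyses.

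SE, AL and exodeviation are explicitly baseline values; outdoor hours carry no time reference. The closing text of section 5.11 (Clinical examinations) says that "Daily outdoor hours and self-report symptoms related to allergy", photophobia and other complaints are asked about at each visit. Table 1 in section 5.10 also ticks a "Daily activity questionnaire" at baseline and at all nine follow-up visits.

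Section 5.6 sizes the trial for the overall treatment difference only.

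**The concern.** There are three separate weaknesses.

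- **Error rate.** Many interaction tests share one unadjusted threshold. A nominally significant result could be reported as an effect modifier when chance explains it.
- **Information.** Age, SE, AL, exodeviation and (if recorded on a scale) outdoor hours are reduced to two levels. This discards information in tests that have little power to begin with.
- **Timing.** If outdoor hours came from follow-up visits, the subgroup could depend on treatment. Photophobia, for example, might change time spent outdoors. The comparison within such a subgroup would no longer be protected by randomisation. Leaving the visit unstated also leaves a choice open after the data are seen.

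At stake is the reading of the subgroup results, not the primary result.

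**Working it through.** **Inputs.** Section 5.6 assumes "the annual reduction of SE as 0.59 D in the 0.01% atropine group and 0.81 D in the control group", a difference of 0.81 - 0.59 = 0.22 D, and "the common standard deviation (SD) is assumed as 0.57 D in each group". It uses 2:1 allocation, 80% power, two-sided 5%, 160 + 80 analysed and 20% drop-out. The modifiers, outcomes and threshold come from section 7.

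**The plan's own figure.** Controls needed = (1.96 + 0.842)² × 0.57² × (1 + 1/2) / 0.22² = 79.03, rounded up to 80, with 160 on atropine. Power at 80/160 is 80.5% (normal approximation) or 80.2% (noncentral t). Enrolment is 240 / 0.80 = 300. The stated sample size reproduces.

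**Number of tests.** 6 modifiers × 3 outcomes = 18 per time point. This is a minimum, because choroidal measures are plural and are counted once here.

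**False positives when no modifier has any effect.**

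- Expected number: 18 × 0.05 = 0.9, whatever the correlation.
- At least one, if independent: 1 - 0.95^18 = 0.603.
- At least one, under assumed correlations (simulation of 18 normal test statistics, 200,000 draws):

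| Correlation between outcomes | Correlation between modifiers | Chance of at least one |
|---|---|---|
| 0.5 | 0.2 | 53% |
| 0.8 | 0.3 | 42% |
| 0.8 | 0.5 | 37% |
| 0.9 | 0.5 | 32% |

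- SE outcome alone (6 tests), if independent: 1 - 0.95^6 = 0.265.

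**Power of a split interaction test for SE, 240 analysed.**

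- Standard error of the overall effect: 0.57 × √(1/80 + 1/160) = 0.078.
- Two equal subgroups: standard error of the difference in effects = 2 × 0.078 = 0.156.
- For a 0.22 D contrast between halves: 0.22 / 0.1561 = 1.41, so power is 29%. It is 25% for a 30/70 split and 20% for a 20/80 split.
- Smallest contrast detectable at 80% power: 2.80 × 0.1561 = 0.44 D, twice the whole assumed treatment effect.
- If all 300 were analysed, power for 0.22 D would be 35% at best. If both eyes are used, with an assumed inter-eye correlation of 0.8, it is about 32% with 240 children.

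**Gain from keeping the modifier continuous.** For a normal modifier, a linear interaction and a median split, the split keeps 2/π = 0.637 of the information. The continuous test then has equivalent standard error 0.1561 × √0.637 = 0.1246. So 0.22 / 0.1246 = 1.77, and power is 42% against 29%.

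**What the fix cannot do.** An 80%-powered test of a 0.22 D contrast between equal halves would need about 317 + 634 = 951 analysed children, roughly four times 240.

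**The case against.** The plan does several things well. Factors and cut-points are specified in advance, and differences are judged by formal interaction tests rather than by comparing p-values within subgroups. No objective in section 4 concerns a subgroup, so no confirmatory claim rests on these tests. Low interaction power is normal in a trial sized for its overall effect. All of this stands, and it limits the point to secondary interpretation. It does not control error across 18 tests, recover discarded information or date the outdoor-hours value.

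Some stronger readings go beyond the documents:

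- **That a false positive is likely.** This needs near-independence. Changes in SE and AL, and baseline SE and AL as modifiers, are plausibly correlated, and at the stronger assumed correlations the chance is below one half. Only the expected 0.9 is free of that assumption.
- **That there are 36 tests, with an 84% chance of at least one false positive** (1 - 0.95^36). This assumes subgroup testing at both 1 and 2 years, and independence. Section 7 names no time point.
- **That cutting in two costs this trial about a third of its information.** The 64% belongs to a normal modifier cut at its median. A uniform modifier would keep 75%, and an off-median cut could keep less. The plan's cuts are fixed values and the documents give no distributions.
- **That the plan forms a post-randomisation subgroup.** It nowhere says so; it leaves the visit unstated. Age also lacks the word baseline, but treatment cannot change it.

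**Conclusion.** The point holds as a cheap improvement to the secondary analyses. About 0.9 false-positive interactions are expected per 18 tests if no modifier matters. The chance of at least one is 60% under independence and about 32% to 53% under the correlations assumed above. The gain from continuous terms, 29% to 42% power, rests on a normal modifier, a linear interaction and a median split; the gain at the plan's actual cut-points cannot be computed from the documents. The missing time reference for outdoor hours is a plain gap in the text that permits, but does not state, a subgroup treatment may have influenced.

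A reader might infer that continuous modelling would make these tests adequately powered, or that the main result is in doubt. Neither follows: 42% is still low, and the primary comparison and its sample size are untouched.

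**What to change.** In section 7:

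1. Test treatment-by-modifier interaction with age, baseline SE, baseline AL and baseline distance exodeviation as continuous terms. Treat baseline outdoor hours the same way if they are recorded on a scale. Keep sex binary.
2. Use the pre-specified cut-points only to display subgroup estimates with confidence intervals.
3. Define outdoor hours as the value collected at the baseline visit. The documents do not say whether the activity questionnaire is its source, so the definition should name the visit and the instrument.
4. State that all interaction tests are exploratory and will be reported as such.

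The exploratory label is preferable to a Holm correction within each outcome. At that procedure's strictest step (0.05/6 = 0.0083), power for a 0.22 D contrast falls from 29% to 11%. Three outcome families each held at 0.05 could still give 1 - 0.95³ = 14% overall if independent, so the 18-test family would not be controlled either.

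The cost is analysis-plan wording; no new data are needed. The downside is that a continuous term assumes a straight-line trend, which the displayed cut-point estimates help to check.
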